#### Daily from day 1 - 5 after inclusion

- Patient in a REDUSE ICU this day (Y/N)
- Resuscitation fluids (Crystalloids administered to correct hemodynamic impairment as noted in the patient chart or given at a rate > 5 ml/kg/h (Ringer's acetate/lactate [ml], 0.9% NaCl [ml], other [ml]; Colloids (Albumin 4-5% [ml], Albumin 20% [ml], other [ml]; Blood products (Erythrocytes [ml], Plasma [ml], Platelets [ml])).
- Intravenous vehicles and drugs (Antibiotics [mL], Inotropes (includes dobutamine, levosimendan, or dopamine <5mcg/kg/min) [mL], Vasopressors [mL], Analgesics [mL], Sedatives [mL], Insulin [mL] and dose [E/24h; If the patient was in the ICU for less than 24 hours this day, extrapolate the dose to 24 hours], Potassium [mL], Other electrolytes [mL], Other drugs [mL], 5% glucose used as a vehicle [mL], Other concentration of glucose used as a vehicle [mL and concentration in %]).
- Maintenance/replacement and nutrition (Crystalloids administered for reasons other than correcting hemodynamic impairment. If indication in the medical charts is unclear, crystalloids at a rate below 5 ml/kg/h will be classified as maintenance fluids (Ringer's acetate/lactate [ml], 0.9% NaCl [ml], other (ml)), Glucose (2.5% [ml], 5% [ml], 10% [ml], 20% (ml), other glucose strength (mL and concentration in %)), was no or 20% glucose given in accordance with established local protocols/routines; Parenteral nutrition (ml); Enteral nutrition (ml); Enteral water (ml); Other fluids (mL); Total caloric intake [including Propofol and glucose solutions] (kcal)
- Diuretics (Loop diuretics/furosemide [mg/24h], Other (type of drug and mg/24h)
- Fluid output (Urinary output [ml], Drains [ml], Haemorrhage [ml], Faeces [if liquid and collected through a faecal management system, ml], Fluid removal in RRT [ml], Other losses [evaporation excluded] (ml)
- Fluid balance (Total fluids that day [mL], Fluid balance [mL], Cumulative fluid balance [mL], Total volume of resuscitation fluids [mL], Total volume of non-resuscitation fluids [mL], Weight [kg], Fluid balance goal for next 24h [Y/N, and volume in mL])
- Creatinine [highest](μmol/L)
- Acute Kidney Injury (Calculated based on creatinine and urine output [Y/N], if yes specify KDIGO score)
- Renal replacement therapy (Y/N)
- Earliest urea (mmol/L; Value closest in time to the change of day at the institution.)
- Lowest MAP (mmHg; Lowest value that day)

- Type of inotropic drug or vasopressor (any dose of dobutamine, dopamine, vasopressin or other V1A agonists, levosimendan, angiotensin II, noradrenaline, adrenaline, milrinone, or other)
- Noradrenaline dose (highest dose during the day;  $\mu\text{g/kg/min}$ )
- Corticosteroid treatment (Y/N)
- Atrial fibrillation/flutter (Y/N)
- Mechanical ventilation (Y/N)
- Lowest PaO2 (kPa)
- FiO2 (at time of lowest PaO2; %)
- Lactate [highest] (mmol/L)
- Sodium [earliest] (mmol/L)
- Potassium [earliest] (mmol/L)
- Chloride [earliest] (mmol/L)
- Blood glucose [earliest] (mmol/L)
- Ischemic events (Y/N) (criteria described above), if yes, specify: a) Limb, b) Cerebral, c) Heart, d) Intestine
- Hypoglycemia (Mild/moderate hypoglycaemia 2.3 - 3.9 mmol/L) (Y/N), Severe hypoglycaemia  $\leq 2.2$  mmol/L) (Y/N)
  - o If yes to severe hypoglycemia:
    - Was the patient receiving IV glucose at the time of the event (Y/N)
    - Was the patient receiving insulin at the time of the event? (Y/N)
    - Was the patient receiving enteral nutrition at the time of the event (Y/N)
    - Additional information/details (free text)
- Hypernatremia [ $>159$  mmol/L] (Y/N)
- Hyperchloremic acidosis [ $\text{pH}<7.15$  and plasma-chloride  $>115$  mmol/L] (Y/N)
- Metabolic alkalosis [ $\text{pH}>7.59$  and base excess  $>9$ ] (Y/N)
- Central venous catheter complications (Includes malfunctions, infections, thrombosis and venous stenosis) (Y/N and specify)
- Suspected unexpected adverse events (SUSAE) (Y/N); (A SUSAE is an adverse event not reasonably explained by other factors than the intervention which may cause death, be life threatening, prolong hospitalisation, or result in significant disability/incapacity.)

Daily from day 6 to discharge from REDUSE ICU or day 90

- Patient in a REDUSE ICU this day (Y/N)
- Fluids (Total volume of resuscitation fluids [mL], Total volume of non-resuscitation fluids [mL], Total fluid output [mL], Fluid balance[mL])
- Ischemic events (Y/N) (criteria described above), if yes, specify: if yes, specify: a) Limb, b) Cerebral, c) Heart, d) Intestine
- Any new Acute kidney injury (Y/N, if yes specify KDIGO score [1-3])
- Hypoglycemia (Mild/moderate hypoglycaemia 2.3 - 3.9 mmol/L) (Y/N), Severe hypoglycaemia  $\leq 2.2$  mmol/L) (Y/N)
- Hypernatremia [ $>159$  mmol/L] (Y/N)
- Hyperchloremic acidosis [ $\text{pH}<7.15$  and plasma-chloride  $>115$  mmol/L] (Y/N)
- Metabolic alkalosis [ $\text{pH}>7.59$  and base excess  $>9$ ] (Y/N)
- Central venous catheter complications (Includes malfunctions, infections, thrombosis and venous stenosis) (Y/N and specify)
- Suspected unexpected adverse events (SUSAE) (Y/N))

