### 3.2 Secondary outcomes

- One or more complications in the ICU defined as one or more of the following events in the ICU:
  - a) Acute cerebral infarction (documented on brain MRI or CT scans) with corresponding neurological symptoms.
  - b) Acute coronary syndrome (defined as acute myocardial infarction or unstable angina pectoris) AND either reperfusion treatment (percutaneous coronary intervention, PCI or thrombolysis) or initiated/increased antithrombotic treatment.
  - c) Acute intestinal infarction (either diagnosed during surgery or by angiography).
  - d) Limb ischemia (defined as clinical signs of limb ischemia AND one of the following treatments: open or percutaneous vascular intervention, amputation, or initiation/increased antithrombotic treatment.
  - e) New onset severe acute kidney injury (defined as stage 3 according to the kidney disease improving global outcomes [KDIGO] criteria [Kellum 2013]).
- Mechanical ventilation-free days within 90 days of inclusion.
- Cognitive function as determined by the Montreal Cognitive Assessment 7.1 BLIND/telephone version (MoCA-BLIND) at 6 months (Pendlebury 2013, Wittich 2010).

- Health-Related Quality of Life as determined by the EQ Visual Analogue Scale (EQ-VAS) at 6 months (Van Reenen 2015).

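### From day 6 the data collection asks only about new AKI, so later progression to KDIGO stage 3 is not reliably captured and cannot be verified

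*Protocol*

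**What the plan says.** Section 3.2, item e, defines the component as "New onset severe acute kidney injury (defined as stage 3 according to the kidney disease improving global outcomes [KDIGO] criteria". It counts if it occurs in the ICU. Table 1 schedules complications from day 1 to ICU discharge, and section 5.2 allows the allocated treatment to run for up to 90 days. Events from day 6 onward are therefore inside the outcome window.

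For days 1-5, Appendix A lists these renal items each day:
- "Creatinine [highest" value
- "Fluid output (Urinary output [ml], Drains [ml], Haemorrhage [ml" and other separate losses
- "Renal replacement therapy (Y/N"
- "Acute Kidney Injury (Calculated based on creatinine and urine output [Y/N], if yes specify KDIGO score"

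For day 6 to discharge from a REDUSE ICU or day 90, the daily renal item becomes "Any new Acute kidney injury (Y/N, if yes specify KDIGO score [1-3". Creatinine and RRT are no longer listed as daily items. Urine is no longer separate, and the form keeps "Total fluid output [mL], Fluid balance[mL".

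After that, the section on data up to 90 days asks for the number of RRT-free days and the latest creatinine recorded at any hospital.

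**The concern.** The outcome is about reaching stage 3. The item used from day 6 is about whether AKI is new. These are different questions, and they diverge for patients whose AKI began at a lower stage and then worsened.

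Such patients are expected: section 10.4 plans a subgroup with AKI of stage 1 or higher at randomisation, and others will develop mild AKI in the ICU.

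The component has a stated safety purpose. Section 3.4 explains that giving less non-resuscitation fluid could reduce intravascular volume and so increase AKI. It also feeds the complications indicator sent to the data safety monitoring committee (Appendix B, sections 9 and 10). If late stage 3 events are missed, the count is too low. If the arms differ in early mild AKI, the shortfall can differ between them. A statistical analysis plan cannot repair this, because the fields needed would not have been collected.

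**Working it through.** The protocol states no figure for this point. The check compares the outcome definition with the data listed to support it.

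**Step 1. What is recorded each day**

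| Item | Days 1-5 | From day 6 |
|---|---|---|
| Highest creatinine | yes | not listed |
| Urine output | separate | only within total output |
| RRT (yes/no) | yes | not listed |
| AKI | present or not, with stage | only if new, with stage |
| Ischaemic events (the other four components) | yes | yes, same item |

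Of the five components, only AKI is asked differently after day 5.

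**Step 2. Following patients through the form, with *new* taken literally**

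| Course | Result on the form |
|---|---|
| Stage 3 reached on days 1-5 | recorded |
| No AKI to day 5, first AKI on day 8 already at stage 3 | yes, stage 3: recorded |
| Stage 1-2 on day 5, stage 3 on day 8 | AKI is not new: no, stage not requested |
| First AKI on day 7 at stage 1, stage 3 on day 9 | day 7 yes, stage 1; day 9 no |

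If *new* is read as a new, higher stage, the last two rows are recorded correctly. The protocol does not say which reading applies.

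Section 3.2 leaves a related question open: whether stage 3 is of new onset in someone who entered the trial with stage 1-2. The gap does not depend on the answer. A patient without AKI at randomisation who has stage 1 on day 3 and stage 3 on day 8 meets the definition either way.

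**Step 3. Whether other fields can fill the gap**

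- RRT-free days to day 90, set against the daily RRT item for days 1-5, can show that RRT was used later. They give no date and are not tied to the ICU stay.
- The latest creatinine within 90 days is a single late value, not the ICU peak.
- Total fluid output cannot be split to give urine output.

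None of these dates a stage 3 event to the ICU stay, so a wrong no cannot be found in the trial database.

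**Step 4. An illustration of size, on assumed rates**

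The first three inputs are assumptions and are not in the protocol:
- stage 1-2 AKI by day 5: 30% to 40%
- still in the ICU afterwards: 40% to 50%
- then progressing to stage 3: 5% to 15%

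From the protocol: 1850 patients (section 10.1.1), a 30% control complication rate and a 20% relative reduction (section 10.1.2).

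Share missed = P(stage 1-2) × P(still in ICU) × P(progress)
- Low: 0.30 × 0.40 × 0.05 = 0.006, and 0.006 × 1850 = 11 patients
- High: 0.40 × 0.50 × 0.15 = 0.030, and 0.030 × 1850 = 56 patients
- Relative to the 30% rate: 0.006 / 0.30 = 2%, and 0.030 / 0.30 = 10%

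This overstates the loss in two ways. It treats every late progression as missed, and it ignores patients who still count through another component. It also leaves out AKI that starts after day 5 and then worsens.

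As a constructed case of unequal loss, suppose early stage 1-2 AKI is 40% in one arm and 30% in the other, with the high values elsewhere. The losses are 0.030 and 0.30 × 0.50 × 0.15 = 0.0225, a difference of 0.75 percentage points. The difference planned for is 0.30 × 0.20 = 6 points.

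**The case against.** The strongest reply is that this is one loose word. The item is asked on every ICU day and offers stages up to 3. A site could sensibly read *new* as a new stage, in line with the outcome definition. Appendix A describes the data and is not the form itself. Sections 6.1 and 8.2 place data-entry instructions in the eCRF, the trial master file and the trial ledger, which are not shown here. Source records are kept for 15 years (section 8.1), so values could be looked up. Stage 3 AKI is one of five components of an outcome that section 10.2 treats as hypothesis generating.

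Much of this stands. A reader might infer that late progression is not captured at all. The protocol does not support that, because a site reading *new* as a new stage would record it. Nor is all renal information lost after day 5: total output continues, and RRT use by day 90 is partly visible. That data collectors are unblinded (section 5.4) applies equally to days 1-5 and is no separate defect of the later form.

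What does not fall away is the mismatch. Section 6 names Appendix A as the detailed description of the data. Its literal wording gives the wrong answer for progression, and the daily values that would expose the error are dropped at the same point.

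**Conclusion.** From day 6, progression from stage 1-2 to stage 3 is not reliably captured and cannot be verified from the collected data. Stage 3 events could be undercounted, and unequally if early stage 1-2 AKI differs between arms. The problem is confined to one of five components of one secondary outcome, and to patients still in a REDUSE ICU after day 5. The primary outcome is untouched.

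The size is unknown because the protocol gives none of the rates needed. The 0.6% to 3.0% of patients shown above rests wholly on assumed rates.

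A reader might go further and infer that a kidney harm of fluid restriction would be masked. That would need more early mild AKI in the restricted arm, with progression only after day 5. The protocol shows no such imbalance, and section 3.4 cites trials of restricted resuscitation fluid that found no effect on AKI or less of it. Masking is possible, not shown. The point is a cheap improvement worth making.

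**What to change.** From day 6, replace the AKI item with *highest KDIGO stage this day (0-3)*. State in section 3.2 and Appendix A what new-onset stage 3 means for patients who already have AKI at randomisation, separately for those at stage 1-2 and those already at stage 3.

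If stage 3 is to be derived centrally by the same rule on all ICU days, blinded to arm, also carry forward the day 1-5 fields for highest creatinine, urine output and RRT (yes/no). Urine output is needed because the day 1-5 calculation uses it; creatinine and RRT alone would not reproduce that rule.

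The cost is one reworded item and, with central derivation, up to three extra fields per ICU day after day 5, all already defined for days 1-5. For any patient past day 5 before the change, the highest stage would have to be completed from hospital records.

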#### At discharge from REDUSE ICU

- ICU discharge (If patient is transferred to a non-REDUSE ICU they will be considered as discharged from the ICU. If the patient is transferred to a REDUSE ICU, this will not be considered an ICU discharge.)

- Date and time of ICU discharge (dd-mmm-yyyy, hh:mm)
- Status at ICU discharge (alive/deceased)
- Length of last ICU stay (hours/days)
- Length of ICU stay (hours/days)

#### -ICU readmission

- Date and time of ICU readmission and discharge (dd-mmm-yyyy, hh:mm)
- Status at ICU discharge (alive/deceased)

- Withdrawal of life sustaining therapies (WLST) (Including any withdrawal of care which results in the patient not receiving the intervention, for example, palliation.) (Y/N), if yes, specify reason:

- Irreversible organ failure (Y/N); if yes specify Cardiac, Lung, Liver, Kidney, Coagulation, Brain or Other
- Medical comorbidity (Y/N)
- Other (Y/N); specify
- Date and time when WLST decision was made (dd-mmm-yyyy, hh:mm)

#### Up to 90 days after inclusion

- Date of follow-up (dd-mmm-yyyy)
- Status (alive/deceased)
- Days alive and free of renal replacement therapy (RRT) (days; Only include full days without RRT. The data should be recorded for up to 90-days regardless of how the patient was discharged or readmitted.)
- Non-invasive and invasive mechanical ventilation-free days (days; Only include full days without invasive or non-invasive mechanical ventilation. Nasal high flow oxygen therapy is not considered mechanical ventilation. The data should be recorded for up to 90-days regardless of how the patient was discharged or readmitted)
- Vasopressor-free days (days) (Only include full days without vasopressors. The data should be recorded for up to 90-days regardless of how the patient was discharged or readmitted.)
- Days spent in any ICU (days) A day with any time spent in any (incl. non-REDUSE) ICU counts as an ICU day, even if it is less than 24 hours. The data should be recorded for up to 90-days regardless of how the patient was discharged or readmitted.)
- Hospital-free days (days; Only count full days out of hospital. Time spent in a rehabilitation facility, long-stay hospital, hospice, or nursing home is considered as time spent out of hospital. Includes any hospital (even non-REDUSE sites). The data should be recorded for up to 90-days regardless of how the patient was discharged or readmitted)
- ICU-free days (days)
- Creatinine at hospital discharge ( $\mu\text{mol/L}$ ; Latest value recorded within 90 days at any hospital)

#### At 6 months

- Date of follow-up (dd-mmm-yyyy)
- Status (alive/deceased)
- Was follow-up completed; if no specify reason (Patient lost to follow-up, Alive but refused to consent to follow-up, Alive but unable to follow-up for other reasons)
- Place of follow up (Institution/ home of patient/ telephone/ digital)
- Montreal Cognitive Assessment (MoCA-BLIND) (telephone). The MoCa blind assess attention and concentration, memory, language, conceptual thinking, calculations and orientation.
- Health-Related Quality of Life (HRQoL) using the European Quality of Life visual analogue scale (EQ-VAS). EQ-VAS is a self-report of overall health and part of the EQ - 5 Dimensions 5 Levels (EQ-5D5L) questionnaire and ranges from 0 to 100.
- HRQoL using the EQ-5D-5L questionnaire. EQ-5D-5L assesses HRQoL in five dimensions (mobility, self-care, usual activities, pain, discomfort and anxiety/depression) where each dimension is rated on a five-levels scale.
- World Health Organization Disability Assessment Schedule 2.0 (WHODAS). WHODAS 2.0 is a patient- or proxy-reported measure of disabilities in 12 aspects of daily life. Each question is answered on a five-level scale.
- Life Satisfaction (ranges from 1-10)
- Background information
  - Does the patient have a native language other than the test language (Y/N); if yes: judgement about whether the patient is sufficiently good at the test language to complete the tests or need interpreter
  - Problem with capabilities that may interfere with the patient's ability to perform the tests (Not including problems with hearing or vision that are corrected for by hearing aid or glasses)
    - No problems
    - Hearing
    - Vision
    - Speech problems
    - Dyslexia
    - Paresis
    - Memory problems or other cognitive problems prior to the episode of sepsis
    - Other
  - Known neurological disease (Y/N; specify) (includes Stroke, Multiple Sclerosis, Parkinson's disease, Dementia etc.)
  - Highest education level (functional equivalent of the indicated options for a given society based on international standard classification of education by UNESCO)
    - No formal education
    - Incomplete primary/lower secondary school
    - Complete primary/lower secondary school
    - Incomplete upper secondary school
    - Complete upper secondary school
    - Some university-level education, without degree
    - University-level education, with degree

- Marital status (married/living together as married, living together with parents/children, or living alone)
- Current place of residence
  - Home
  - Hospital
  - Rehabilitation centre
  - Nursing home
  - Other
- Occupational status before the episode of sepsis
  - Working full-time
  - Working part-time
  - Unemployed
  - Retired due to age
  - Retired due to disability / health problems
  - On sick leave
  - Other (e.g., student, housewife)
- Occupational status at the time of the follow-up
  - Working full-time
  - Working part-time
  - Unemployed
  - Retired due to age
  - Retired due to disability / health problems
  - On sick leave
  - Other (e.g., student, housewife)
  - Date of return-to-work (if applicable)
- Rehabilitation after the episode of sepsis
  - None
  - Inpatient rehabilitation
  - Outpatient rehabilitation
  - Home-based rehabilitation (community)
  - Physiotherapist only
  - Occupational therapist only
  - Counselling (by e.g., social worker or psychologist)
  - Cognitive Behavioural Therapy
  - Other
- Glasgow Outcome Scale Extended (GOSE) modified for use after Sepsis. GOSE is a clinician-reported global functional outcome scale with 8 ordinal categories, ranging from dead (1) to upper good recovery (8) based on a structured interview with the patient, proxy (e.g., a relative or close friend) or both
- Modified Fatigue Impact Scale (MFIS). MFIS is a patient-reported measure of fatigue and consists of 21 questions. Each question is answered on a five-level scale.
- Patient Questionnaire regarding scope, completeness, and timing of follow up. The questions are answered on a five-grade Likert scale or as yes/no
  - How do you feel the questions have allowed you to describe your experiences after sepsis
  - Do you feel that any questions are missing about symptoms/difficulties which affect your everyday life post sepsis

- Which is your overall experience of the follow-up
- How would you describe the timing of the follow-up
- Have you been offered a similar follow-up after your episode of sepsis from healthcare

At 1 year

- Date of follow up (dd-mmm-yyyy)
- Survival status at 1 year (alive/deceased/unknown)

Death

Date and time of death (dd-mmm-yyyy, hh:mm)

## **Appendix B. Charter for the Data Safety and Monitoring Committee (DSMC)**

### **1. Introduction**

This Charter defines the primary responsibilities of the DSMC, its relationship with other trial components, its membership, and the purpose and timing of its meetings. The Charter will also provide the procedures for ensuring confidentiality and proper communication, and the statistical monitoring guidelines to be implemented by the DSMC.

### **2. Primary responsibilities of the DSMC**

The DSMC will, jointly with the steering group, be responsible for safeguarding the interests of trial participants and assessing the safety and efficacy of the interventions during the trial. The DSMC will recommend stopping or continuing the trial to the steering group of the REDUSE-trial. The steering group will be responsible for promptly reviewing the DSMC recommendations, deciding whether to continue or terminate the trial and determining whether amendments to the protocol or changes in trial conduct are required. The DSMC is planned by protocol to meet (physically or online) to evaluate the planned interim analysis of the REDUSE-trial. A statistician selected by the DSMC will perform the interim analyses. The recommendations of the DSMC regarding stopping, continuing, or changing the design of the trial should be communicated without delay to the steering group. The steering group has the responsibility to inform all investigators participating in the trial of the recommendation of the DSMC and the subsequent steering group decision as soon as possible and no later than 48 hours after the decision is made.

### **3. Members of the DSMC**

The DSMC is an independent multidisciplinary group consisting of clinicians and a biostatistician that, collectively, have experience in managing ICU patients and in conducting, monitoring and analysing clinical trials.

### 4 Conflicts of interest

DSMC membership has been restricted to individuals free of financial, scientific, or regulatory conflicts of interest. Any DSMC members who develop significant conflicts of interest during the trial should resign from the DSMC. DSMC membership is to be for the duration of the clinical trial. If any members leave the DSMC during the trial, the steering group will appoint their replacement(s).

